#### Biochemical studies

Fasting blood tests will be performed at baseline, weekly during radiotherapy (visits 2–10, 1 day prior to chemotherapy if receiving) and at 6, 12 and 18 months in all patients. Patients allocated to the MHP high-risk arm and started on oral bisphosphonate therapy will have an additional bone turnover marker blood test at 3 months to assess bisphosphonate efficacy. All samples will be taken simultaneously with routinely collected clinical blood samples where appropriate.

As part of the MHP intervention arm, blood will be sampled, analysed and assessed at baseline, 6, 12 and 18 months for the measurement of full blood count, urea and electrolytes, liver function tests, parathyroid hormone, vitamin D, thyroid function test, oestradiol, haemoglobin A1c, procollagen type 1 amino-terminal propeptide (P1NP) and the beta-C-terminal telopeptide (CTX). Moreover, in the observation arm, serum samples will be collected, processed and stored at −80°C for batch analysis at the end of the study.

Additional fasting blood samples will be collected at all timepoints mentioned for longitudinal analysis of bone turnover markers and for proteomic analysis. These samples will be processed and stored at −80°C, following local standard operating procedures (SOPs), for batch analysis at the end of the study. Bone turnover markers will be evaluated using ELISA techniques and will include CTX, N-terminal telopeptide (NTX), P1NP, osteocalcin, Tartrate-resistant acid phosphatase 5b (TRAcP5b) and bone alkaline phosphatase (ALP).

#### Sequential Window Acquisition of all Theoretical Mass Spectra

Proteomic analysis will be conducted at the Stoller Biomarker Discovery Centre, following local SOPs.^15^ Samples will be analysed by a data independent acquisition method known as Sequential Window Acquisition of all Theoretical Mass Spectra (SWATH-MS) with a microflow liquid chromatography-mass spectrometry system comprising an Eksigent nanoLC 400 autosampler and an Eksigent nanoLC pump coupled to a SCIEX 6600 Triple-TOF mass spectrometer (68 min run-time). When SWATH maps are generated, the presence and abundance of plasma proteins will be quantified using published plasma reference libraries. Differential expression analysis will be used to identify candidate biomarkers using artificial intelligence approaches. Linear regression will be used to detect correlations with the presence of RRIFs and BMD.

Few longitudinal studies have tracked proteins of interest over the whole course of radiotherapy from pretreatment baseline through to follow-up. We have undertaken one pilot that shows the potential value of this work.^16^ Other studies that have investigated this have demonstrated distinguishing profiles with groups of approximately n=30. Two preradiotherapy baseline samples will be used to assess natural variation and comparison with the variance of measurements following radiotherapy and further comparison between the MHP and observation arm (n=40 per group).

Electronic data will be pseudoanonymised (coded) to protect the identity of the participants.

#### PROMs and health utilisation proforma

PROMs will be collected either as electronic PROMs (using the myChristie, myHealth application) or paper-based PROMs at baseline 6, 12 and 18 months.

The evaluated PROMs will include the adapted pelvic patient-reported outcome version of the common terminology criteria for adverse events (PRO-CTCAE) assessment, the Short Musculoskeletal Function Assessment (SMFA) modified for lower limb, the 5-level version of the EuroQol tool (EQ-5D-5L) and a tailored health utilisation proforma.

The CTCAE pelvic questionnaire will include as measures bowel questions scored out of 22, urinary questions out of 19 and sexual questions out of 8, with a total out of 49; a higher score indicates worse QOL. The adapted SMFA questionnaire includes 39 questions, with a minimum possible score of 39 and maximum of 195; scores are standardised with high scores indicating poor function.

### Criteria for discontinuing

Participants may decide to withdraw from the study at any time. Discontinuation of the study participants may occur as a result of investigator decision, safety concerns and significant non-compliance to the protocol or incorrect enrolment. Reasons for discontinuation will be captured.

As this is a feasibility study, participants may decide to discontinue their participation in certain aspects of the study (eg, declining the prehabilitation programme or deciding not to take recommended medications). The participants can continue with the study and the details will be captured in the case report form.

### Outcomes

The primary outcomes for this feasibility study will inform the design and power calculations for a definitive UK multicentre RCT. These are:

Eligibility and screening rate: proportion of patients eligible for the study from patient population (assessed at baseline).Recruitment and study group allocation rate: number and proportion of eligible patients recruited, randomised and allocated to appropriate study populations (assessed 2 weeks postconsent).Intervention fidelity rate: number and proportion of patients completing the elements of the study (assessment visits, prehab exercise programme, prescribed medications, QOL questionnaire) (assessed at the end of study, at 18 months).Attrition rate: number of patients lost to follow-up (assessed at the end of study, at 18 months).Patient and physician acceptability assessed with electronic questionnaires (change from baseline assessed at 6, 12 and 18 months).Health economic analysis: within-trial cost-effectiveness analysis to demonstrate feasibility of health economic data collection and analysis in a multicentre RCT (change from baseline assessed at 6, 12 and 18 months).

The secondary outcomes are:

Incidence of pelvic RRIF (assessed at 6, 12 and 18 months postradiotherapy).Longitudinal change in BMD and fracture risk using FRAX (assessed at baseline and 18 months).Longitudinal change in biochemical markers of bone turnover (change from baseline assessed at 2, 3, 4, 5, 6, 7, 8 and 9 weeks and at 6, 12 and 18 months).QOL assessment: adapted CTCAE pelvic questionnaire and SMFA adapted to lower limbs (change from baseline assessed at 6, 12 and 18 months).

Exploratory end points include identification of predictive markers of RRIFs (radiomic, proteomic, BMD) and exploratory measurement of proteomic biomarkers of bone turnover during pelvic radiotherapy.

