#### Prehabilitation exercise programme (Prehab4Cancer)

All patients randomised to the MHP arm of the study will be offered a bespoke prehabilitation exercise programme via the Prehab4Cancer programme in Greater Manchester. The MHP arm patients will be referred to the Prehab4Cancer team via electronic referral immediately following randomisation. Allocated patients will be individually assessed by the Prehab4Cancer team according to their usual protocols and assigned an appropriate prehabilitation programme. Duration of the programme is 12 weeks from the first assessment and participation will be encouraged, as tolerated. The Prehab4Cancer and recovery programme is community-based, which incorporates exercise (cardiovascular and muscle strengthening/resistance training), nutritional screening and advice and well-being support. Further details of programmes’ assessment tools and the stratification of interventions are described by Moore *et al*^14^ and can be found in www.prehab4cancer.co.uk. The current scope of this protocol is to evaluate feasibility of participants’ engagement in this face-to-face and remote prehabilitation service both pretreatment and during treatment.

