### Baseline and follow-up evaluation

As described in figure 2, baseline evaluations will include a bone health assessment with DXA BMD measurement and completion of a bone health questionnaire. PROMs will also be captured. Finally, fasting serum and plasma blood samples will also be collected.

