### Data collection, management and analysis

#### Statistical and health economic analysis

As this is a feasibility study, it will not involve hypothesis testing to identify whether the intervention has had an impact. Instead, data analysis will be descriptive, focusing on the percentage of patients in each group developing RRIFs and risk factors for this. Means and a measure of variation will be calculated for each secondary outcome. These data, along with estimates of recruitment and attrition rates, will help inform a power calculation for the definitive trial.

A within-trial cost-effectiveness analysis^18^ will be undertaken from the perspective of the UK NHS. Cost data for the intervention arm will reflect resource use associated with the MHP and treatment costs for both the control and intervention arm will be taken into account. Resource use will be extracted from patient records and the healthcare utilisation proforma. Relevant sources (eg, NHS reference costs) will be used to identify unit costs. Health-related QOL scores will be generated using the EQ-5D-5L at baseline and at each of the three follow-up time points (6, 12, 18 months).

A descriptive analysis of the costs and outcomes data will be completed focusing on: (a) whether the EQ-5D-5L and SMFA are able to adequately capture differences in health status before and after implementation of the MHP and across both treatment arms of the study; (b) whether the resource-use survey is able to record data necessary to enable a full cost-effectiveness analysis; (c) the nature of missing data for the EQ-5D-5L, SMFA and resource-use survey to assess responses, sensitivity and any patterns within the missing data.

A within-trial cost-effectiveness analysis will be conducted to provide an indicative estimate of cost-effectiveness. Between-arm differences in costs and outcomes will be expressed as an incremental cost-effectiveness ratio (ICERs): the cost per quality-adjusted life year gained from the intervention compared with usual care. ICERs will also be calculated using the SMFA in an additional scenario analysis.

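### Primary outcome acceptability is set as change from baseline, but the package does not exist for patients at baseline and a change score cannot show whether it is acceptable

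*Protocol article*

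**What the plan says.** The Outcomes section of the protocol article lists six primary outcomes. The fifth is "Patient and physician acceptability assessed with electronic questionnaires (change from baseline assessed at 6, 12 and 18 months"). The sixth, the health economic analysis, carries the same tag: "feasibility of health economic data collection and analysis in a multicentre RCT (change from baseline assessed at 6, 12 and 18 months"). The identical tag also appears on the secondary quality-of-life outcome.

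On delivery, the section on the Prehab4Cancer programme says "The MHP arm patients will be referred to the Prehab4Cancer team via electronic referral immediately following randomisation". The Interventions section gives the package to the MHP arm only; the observation arm receives standard assessment and care.

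On baseline measurement, the article says "baseline evaluations will include a bone health assessment with DXA BMD measurement and completion of a bone health questionnaire", and adds patient-reported outcome measures (PROMs) and blood samples. The PROMs are the pelvic PRO-CTCAE, the modified SMFA, "the 5-level version of the EuroQol tool (EQ-5D-5L) and a tailored health utilisation proforma". Neither list names an acceptability questionnaire.

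On the economic analysis, the statistical section says "Between-arm differences in costs and outcomes will be expressed as an incremental cost-effectiveness ratio (ICERs"). It also collects EQ-5D-5L at baseline and at each follow-up, and plans a description of health status before and after the package.

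**The concern.** The Abstract and the end of the Introduction both state that the trial is to determine whether the package is acceptable. That is a question about level: do those who received or delivered the package find it acceptable? The metric fixed for this outcome concerns movement since a time when nobody had received the package. If the primary result is reported as defined, readers would learn whether ratings rose or fell, but not whether they were good enough to justify a multicentre trial.

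The tag also sits on the economic outcome, where it fits some components and not others.

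**Working it through.** **Acceptability: the text side by side**

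1. Who can rate the package at baseline? Referral follows randomisation, and bone treatment depends on the risk group assigned within the MHP arm. Before that, an MHP-arm patient can state only an expectation. An observation-arm patient never receives the package.
2. Is a baseline construct named? Not in the sections on baseline evaluation or on PROMs. Figure 2, which holds the schedule, is not shown, so its content cannot be checked.
3. What does the metric return? Let A(0) be a baseline rating and A(t) the rating at 6, 12 or 18 months. The outcome as written is D(t) = A(t) − A(0).
   - Rated high throughout: A(t) = A(0) = high, so D(t) = 0.
   - Rated low throughout: A(t) = A(0) = low, so D(t) = 0.
   - High hopes, good but slightly lower experience: D(t) < 0 although the package is acceptable.
   - Low hopes, poor but slightly better experience: D(t) > 0 although it is not.

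   Neither the size nor the sign of D(t) identifies an acceptable package. A(t) does.
4. Is the level available? Yes. D(t) cannot be formed without A(t), so follow-up ratings must be collected in any case.

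**Precision of the level**

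The Sample size section gives 40 per arm and 15% attrition: 40 × (1 − 0.15) = 34, which agrees with its statement that at least 30 remain. For a proportion among MHP-arm patients, the largest 95% half-width (normal approximation, proportion 0.5) is 1.96 × √(0.25/n):

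| n | half-width |
|---|---|
| 34 | 0.168 |
| 30 | 0.179 |

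This is no worse than about 17 to 18 percentage points, which is usable for a feasibility aim. The number of physicians is not given in the article, so no such figure can be shown for them.

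**Economic outcome**

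The Outcomes section says change from baseline; the statistical section says between-arm differences. To see what depends on baseline, assume QALYs are the trapezoidal area under EQ-5D-5L utility at 0, 0.5, 1 and 1.5 years (the article states no method).

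- Weights on the four visits: 0.25, 0.50, 0.50, 0.25, with sum 1.5. Baseline utility therefore enters the QALY.
- Weights if utility is taken as change from baseline: 0.25 − 1.5 = −1.25 at baseline, then 0.50, 0.50, 0.25.
- Illustration, constant baseline imbalance of 0.03 and no effect: raw area 0.03 × 1.5 = 0.045 QALY; change scale 0.000.
- Illustration, equal baselines and a gain of 0.03 from month 6: 0.03 × (0.50 + 0.50 + 0.25) = 0.0375 on either scale.

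So change from baseline is a meaningful description of utility and can be built into the QALY. It does not describe costs accrued over 18 months, nor the ratio itself.

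**The case against.** The best defence of the acceptability wording has four parts.

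- The parenthesis after each outcome mainly gives assessment times, and this one is identical to that on the quality-of-life outcome, so it may be timing text carried across. That is plausible, but the words name a metric for a primary outcome, and an analyst would be entitled to follow them.
- Anticipated acceptability can be asked before delivery, and a baseline item may appear in Figure 2. This stands, so it would be too strong to say that no baseline can exist. But a shift from expectation to experience still does not give the level.
- Nothing says that levels will go unreported. This is true, and the criticism is of the defined outcome, not a prediction of the eventual report.
- An analysis plan may add detail. It may, but the metric is already fixed here.

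A reader might go further on the economic side. The documents do not support these readings:

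- *That the QALY difference is unadjusted.* The statistical section says only that it is a between-arm difference. It is silent on covariates, which an article may leave to an analysis plan.
- *That the economic outcome is wrong as a whole.* Baseline EQ-5D-5L is collected and a before-and-after description is planned, so part of the tag is apt.
- *That the SMFA-based ratio will make a beneficial package look dominated.* The article does say "scores are standardised with high scores indicating poor function", but nowhere that the unreversed difference is the denominator. Reversal is routine coding.

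The economic stakes are also modest: the stated purpose is a "within-trial cost-effectiveness analysis to demonstrate feasibility of health economic data collection and analysis in a multicentre RCT", and the ratio is described as indicative only.

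**Conclusion.** The acceptability point holds. One of six primary outcomes, tied to a headline aim, is defined by a metric that cannot separate a package acceptable throughout from one unacceptable throughout. No numerical size attaches to it and no sample size changes. The conclusion rests on the text as shown: delivery after randomisation, in one arm only, with no baseline acceptability measure named. If Figure 2 or the full protocol does schedule a baseline item, that item measures expectation and the conclusion is unchanged.

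The economic point is a minor note on wording: the tag is imprecise for costs and for the ratio, and the Outcomes and statistical sections should agree. The QALY figures in the working are illustrations under an assumed method and do not measure any error in the plan.

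**What to change.** 1. Redefine the fifth primary outcome as the level of acceptability at 6, 12 and 18 months among MHP-arm patients and physicians, for example the proportion rating the package acceptable with a 95% confidence interval. State the rating that counts as acceptable before the data are examined.
2. If a baseline item is asked, label it as expectation and show it separately.
3. Reword the sixth primary outcome as completeness of the cost and EQ-5D-5L data, plus between-arm differences in cost and QALYs to 18 months, so that it matches the statistical section.
4. As a recommendation rather than a correction, use the baseline EQ-5D-5L already collected as a covariate for the QALY difference.

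The cost is revised wording for two outcomes and, if the recommendation is taken up, one covariate in one model. No new data collection is needed, because any change score already requires the follow-up ratings.

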### Sample size

No formal power calculation has been performed as this is a feasibility study. The study will collect initial data such as measures of location and variability for key outcome measures. It is recognised that in general, 30 patients are required in order to estimate such parameters.^17^ For this study, a total of 80 patients will be recruited and randomised with equal probability to either the MHP or observation arms (ie, 40 per group). Assuming attrition rates of 15% per group, at least 30 should remain in each arm. This should be sufficient to assess the feasibility of a larger RCT study and estimate group means, SD and percentages for key outcomes.

### Recruitment

Eighty patients will be recruited over an 18-month period, approximately 4 patients per month. As this is a feasibility study, there will be no interim analysis of study results.

### Assignment of interventions

Consenting, eligible participants will be randomised to the MHP or observation group using a validated online service; sealedenvelope (https://www.sealedenvelope.com). A permuted block (block size: 4) randomisation protocol will be used with a 1:1 allocation (MHP to observation arm).

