**Trial registration number:**

NCT04555317.

Strengths and limitations of this studyThe RadBone is the first randomised controlled trial to assess a musculoskeletal health package aimed to prevent radiotherapy-related insufficiency fractures.A feasibility economic evaluation will allow future assessment of this complex intervention’s cost-effectiveness.Planned longitudinal proteomic analyses may reveal mechanistic insights and promising treatment targets.A prospectively published detailed protocol increases the transparency and allows for peer review of the methodology used.This study is not blinded and lacks an active comparator, hence, it is susceptible to performance and detection bias.

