The RadBone is the first open-label prospective randomised controlled trial (RCT) to determine the feasibility and acceptability of a musculoskeletal health package (MHP) intervention in women undergoing pelvic radiotherapy for gynaecological malignancies and inform power calculations for a definitive RCT. Moreover, this feasibility trial will also explore potential implications on the incidence of RRIFs, QOL and other clinical effectiveness and safety outcomes, as well as providing indicative estimates of the intervention’s cost-effectiveness.

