### Study setting

The planned study is a prospective randomised controlled feasibility trial of 80 patients with gynaecological malignancy (cervical and endometrial) undergoing pelvic radiotherapy at the Christie Hospital NHS Foundation Trust in Manchester, UK (a tertiary referral oncology centre). The study opened for recruitment in May 2021, and the estimated primary completion date is in November 2022 and study completion date in June 2023.

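### A single stated block size of 4 in a one-centre, open-label trial makes an expected third of allocations predictable to staff who know the size and track the sequence

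*Protocol article*

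**What the plan says.** Under Assignment of interventions, participants are to be "randomised to the MHP or observation group using a validated online service", and "A permuted block (block size: 4) randomisation protocol will be used with a 1:1 allocation". That section mentions no variation in block size, no stratification factor and no withholding of the size from those who recruit.

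Other sections describe the setting:

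- Study setting gives one hospital.
- Sample size gives 80 patients, 40 per arm. Recruitment gives an 18-month period at about four patients a month.
- The Introduction calls the trial open-label. The strengths and limitations list says: "This study is not blinded and lacks an active comparator, hence, it is susceptible to performance and detection bias". It does not name selection bias.
- The Prehab4Cancer section says: "The MHP arm patients will be referred to the Prehab4Cancer team via electronic referral immediately following randomisation".
- The blinding described under Interventions concerns the observation arm's evaluation results. It does not conceal the allocation.

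**The concern.** An online service hides the list, but it cannot stop staff from deducing the next entry from past ones. Deduction needs three things: a known block size, one sequence to follow, and visible past allocations. The design supplies the second and third. There is one centre with no stated strata, and each arm becomes apparent soon after randomisation. At about four patients a month, a block lasts roughly a month and is easy to count. The first condition depends on who knew the size, and the article has now published it.

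A recruiter who knows the next arm can, even without intending to, bring forward, delay or discourage an approach. Women who seem keen on exercise might be approached when an intervention place is due. Completion of the exercise programme is part of the fidelity outcome, and fidelity and attrition are primary outcomes. The analysis section also reports the percentage with insufficiency fractures in each group and a cost-effectiveness ratio built from between-arm differences. It uses the secondary-outcome data with the recruitment and attrition estimates to help inform the definitive trial's power calculation.

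**Working it through.** **Inputs.** Block size 4 and 1:1 allocation (Assignment of interventions); 80 patients, 15% attrition (Sample size); recruitment opened May 2021 (Study setting) for 18 months (Recruitment); article dated 14 June 2022.

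**The plan's own figures.** 80 / 2 = 40 per arm, and 80 / 4 = 20 complete blocks. 40 × (1 − 0.15) = 34, which agrees with the stated minimum of 30 retained per arm. The article gives no figure for predictability.

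**Allocations determined in advance, fixed block of 4.** There are 6 equally likely sequences with two places per arm. A place is determined once one arm's two places are used up.

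- Fourth place: determined in 6 of 6.
- Third place: determined in 2 of 6 (AABB, BBAA).
- Expected per block: 1 + 1/3 = 4/3, and (4/3) / 4 = 33.3%.
- Over 20 blocks: 20 × 4/3 = 26.7 of 80, with SD √(20 × 1/3 × 2/3) = 2.1. The possible range is 20 (25%) to 40 (50%).

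**Best-guess accuracy.** The recruiter guesses the arm with more places left and tosses a coin when they are equal.

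- First place 1/2; second place 2/3.
- Third place: 1/3 × 1 + 2/3 × 1/2 = 2/3.
- Fourth place 1.
- Mean: (1/2 + 2/3 + 2/3 + 1) / 4 = 70.8%, against 50% under simple randomisation.

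**If the size became known only through the article.** Publication falls at about month 13 of 18. At a uniform rate, 80 × 5/18 = 22.2 patients remained, and 22.2 / 3 = 7.4 allocations would be determined.

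**Effect of alternatives.** The fixed sizes were enumerated exactly. The varying sizes were simulated (3,000 lists of 80), with a recruiter who knows the set of sizes but not their order and updates after each allocation. The sets are illustrative assumptions.

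| Scheme | Known with certainty | Best-guess accuracy |
|---|---|---|
| Fixed 4 (as stated) | 33.3% | 70.8% |
| Fixed 6 | 25.0% | 68.3% |
| Fixed 8 | 20.0% | 66.6% |
| Random 4, 6 | 5.4% | 69.2% |
| Random 2, 4, 6 | 4.1% | 70.1% |
| Random 4, 6, 8 | 2.3% | 67.9% |

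Varying the size removes nearly all certainty. It changes overall guessability little, because most of that comes from blocking itself.

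**Balance.** With blocks of 4, 80 patients fill 20 blocks exactly, so the final difference between arms is 0. With sizes up to 8, the last block may be cut off after as many as four places of one arm, so the difference can reach 4.

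**The case against.** The strongest reply is that the one-third figure is conditional. It needs staff who know the size, know that it does not vary, and follow every allocation. The article does not say who runs the online service or whether recruiters were told the size. It condenses a fuller protocol, so its silence proves nothing either way. This stands, and the figure must carry its condition. What remains is that a single size is stated outright, and the setting makes tracking easy.

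A second reply is that the consequences are limited. The analysis is descriptive with no hypothesis test, so no type I error is affected. Eligibility and recruitment rates are whole-cohort proportions rather than contrasts between arms. This also stands. The exposed figures are the arm-level ones: fidelity, attrition, fracture percentages and the indicative cost-effectiveness ratio.

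Third, the remedy lowers best-guess accuracy by only about three percentage points. That is correct; the gain lies in removing certainty.

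A reader might go further and infer three things that the article does not support:

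- That recruiters did know or use the next allocation. Nothing in the article shows this.
- That nothing can be done at analysis. Baseline characteristics of predictable and unpredictable allocations can be compared, although this cannot see unmeasured motivation or fitness.
- That leaving out tumour site as a stratum is an error. The Introduction's remark that reported incidence varies with tumour type does not make it one in an 80-patient feasibility trial.

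**Conclusion.** The point holds in conditional form. A stated design choice leaves an expected 33% of allocations (about 27 of 80) determined in advance, with 71% best-guess accuracy, for staff who know the size and track the sequence. If the article was their only source and accrual was uniform, the exposure is about 7 of the last 22 or so patients. That the size is fixed is inferred from the single value given.

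The resulting risk is selection bias in the arm-level descriptive results, a route that the stated limitations do not name. It does not invalidate a feasibility study, but it is avoidable at low cost and worth correcting.

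**What to change.** **If recruitment is open:** for the remaining allocations, set the online service to randomly varying block sizes, for example 4, 6 and 8. Withhold the sizes from recruiting staff and from publication until accrual ends. Start the new list where a block of four has been completed. Suggested wording: *Remaining allocations use permuted blocks of randomly varying size; the sizes are not disclosed to staff who recruit or consent participants.*

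**If recruitment is closed:** add selection bias through predictable allocation to the stated limitations. Classify each allocation as predictable or not from its position and the earlier entries in its block, then compare baseline characteristics between the two classes. Show the comparison by arm, since steering in opposite directions could cancel when the arms are pooled.

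**Cost:** a new list for the remaining places, a sentence in the protocol, and a possible final imbalance of up to 4 patients instead of 0 at 80.
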